## 4. Material and Methods

### 4.1. Trial (Study) Design

This is a single-center study prospective, randomized, placebo-controlled trial with three parallel groups of adult patients (18 to 70 years) who have degenerative spinal disorders, specifically those diagnosed with lumbar or cervical spondylosis who are scheduled to undergo spinal fusion, discectomy, decompression, or stabilization procedures. Relevant surgical variables, including cervical/lumbar/thoracic location, type of surgery, surgical approach, duration of surgery, and perioperative complications, will be prospectively recorded and considered in adjusted analyses. The study assesses the influence of a single preoperative VR (exposure) session and its effect on both preoperative and postoperative anxiety and pain, as well as reported functional outcomes in patients undergoing elective spine surgery.

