### 4.3. Participant Sample and Sample Size

#### 4.3.1. Recruitment and Allocation

The sample size calculation is based on detecting a clinically meaningful reduction in preoperative anxiety measured by the State-Trait Anxiety Inventory–State (STAI-S) score, which is the primary endpoint. The trial was powered based on the primary endpoint of STAI-S change. Prior VR perioperative studies report a mean reduction of 8–10 points with a standard deviation of approximately 10 points. Using Rosner’s formula for three parallel study arms, with α = 0.05, power = 0.80, and a minimum clinically significant difference of 8 points, 42 patients per arm are required. To account for an anticipated 15% attrition rate, we will enroll 50 participants per arm, for a total sample size of 150 patients. Elective procedures are defined as those happening the day after the initial patient evaluation. All patients will be provided with written informed consent, and the trial procedures will be explained verbally and in writing to all patients prior to study enrolment.

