### 4.4. Randomization

Eligible patients will be randomly assigned to the VR group, the control group (standard preoperative care), and the VR relaxation/distraction group. Randomization will be performed using a computer-generated permuted block randomization sequence (block size = 6) created by a statistician not involved in patient recruitment or assessment. Allocation concealment will be ensured using sequentially numbered, opaque, sealed envelopes opened only after enrolment. Participants cannot be fully blinded to VR exposure; however, they will be informed that two different VR experiences are under investigation without emphasis on superiority. Outcome assessors and data analysts will remain blinded to treatment allocation. An active comparator VR relaxation/distraction group is included to minimize expectancy and attention-related bias.

After obtaining the patients’ consent and agreement to undergo surgery, the randomization and allocation sequence will be carried out blindly by an independent research assistant during the clinic visit. The researcher conducting interviews and collecting the primary and secondary outcome data will be blind to the group assignments.

To minimize selection bias, randomization will be performed by an investigator independent of patient recruitment and assessment, and outcome assessors and data analysts will remain blinded to group allocation. Participants will be informed that both interventions are active and under evaluation without emphasis on superiority. To reduce the risk of dropout, all participants will receive equal attention and standardized information regarding the importance of study participation. The VR intervention will be administered on the day prior to surgery in a quiet preoperative preparation room.

To prevent any setbacks, a limited number of people will be included to interact with the patients, and a reminder will be given to the patients not to discuss the trial procedure and allocations. In addition, the experiment room will be different from the regular patients’ rooms. In the experiment room, the patients will be exposed to VR content, with respective psychological and physiological assessments. After that, the patients will be instructed to go back to their hospital rooms.

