### 4.5. Instruments and VR Utilization

The study affects all three groups, and the VR intervention includes only one session. All intervention sessions will be carried out individually. After these assessments, the patients will be oriented to the VR goggles and headset and given tutorials and instructions on how to use the device and how to remove it when they encounter potentially unwanted side effects such as dizziness, headache, nausea, or vomiting. In such cases, the procedure will be stopped and considered a withdrawal.

On the day before surgery, following baseline assessment and informed consent, the researcher will randomly allocate the patients to the VR group, control group, and VR relaxation/distraction group.

The study timeline will proceed as follows: enrollment and informed consent → baseline psychometric and pain assessments → randomization → VR or standard-care intervention on the day before surgery → immediate postintervention assessment → surgery → postoperative assessment within 24 h and analgesic assessment within 24–48 h postoperatively.

VR-related adverse effects, including dizziness, nausea, headache, cybersickness, and visual discomfort, will be prospectively recorded and analyzed descriptively throughout the intervention period.

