### 4.8. Data Collection

#### Baseline Value Measurement

On the day before surgery, after informed consent is obtained, evaluations, which include sociodemographic data and the psychometric questionnaires (STAI-S, PSS-10, BDI-II), pain score (VAS), and satisfaction (EVAN-G), will be collected by the researcher before the VR experience (see Table 3).

Perioperative anesthesia and analgesia management will follow standardized institutional protocols whenever feasible. Variables including anesthetic technique, intraoperative opioid administration, postoperative opioid consumption, rescue analgesic use, surgery duration, and perioperative complications will be prospectively recorded and considered in adjusted secondary analyses.

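### The protocol gives three accounts of who randomises, one of which may make the allocator the blinded assessor; separately, a fixed block of 6 lets anyone who tracks the block know 20% of allocations

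*Protocol article*

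**What the plan says.** **Who randomises, and when.** The article gives three accounts.

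- Section 4.4, second paragraph: "the randomization and allocation sequence will be carried out blindly by an independent research assistant during the clinic visit". This follows consent.
- Section 4.4, third paragraph: "randomization will be performed by an investigator independent of patient recruitment and assessment". No time is given.
- Section 4.5: "On the day before surgery, following baseline assessment and informed consent, the researcher will randomly allocate the patients".

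**Who collects data.** Section 4.4 says: "The researcher conducting interviews and collecting the primary and secondary outcome data will be blind to the group assignments". Section 4.8 says that the baseline questionnaires and pain score "will be collected by the researcher before the VR experience", on the day before surgery.

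**Order of events.** The timeline in section 4.5 runs consent, baseline, randomisation, session, post-session assessment. Section 4.4 ties the opening of envelopes to enrolment and does not mention baseline.

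**The sequence.** Section 4.4 specifies a "computer-generated permuted block randomization sequence (block size = 6"), prepared by a statistician with no part in recruitment or assessment and held in numbered, opaque, sealed envelopes. Section 4.1 describes the design: "This is a single-center study prospective, randomized, placebo-controlled trial with three parallel groups". Section 4.3.1 gives the size: "we will enroll 50 participants per arm, for a total sample size of 150 patients". No stratification is described. Section 4.4 accepts that participants cannot be fully blinded, and claims blinding for outcome assessors and analysts.

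**The concern.** A person who opens the envelope knows the arm. If that person also collects outcomes, the stated assessor blinding fails. Site staff need to know from the protocol which of the three accounts to follow, and one of them, taken literally, conflicts with the blinding statement.

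Timing matters because baseline STAI-S is both the start of the primary change score and the covariate in the primary ANCOVA (section 4.9). The score is self-reported by patients who can tell whether they are to receive VR. A baseline taken after the patient learns the arm could differ between arms for that reason alone, and adjusting for it would carry the difference into the primary contrast.

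The block design matters for a different reason. If whoever decides on enrolment can work out the next arm, that person can, knowingly or not, time or withhold the approach to a patient. Envelopes hide the next card. They do not hide what the previous cards imply.

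**Working it through.** **1. The three accounts side by side**

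| Source | Allocator | Time |
|---|---|---|
| 4.4, second paragraph | independent research assistant | clinic visit, after consent |
| 4.4, third paragraph | investigator independent of recruitment and assessment | not given |
| 4.5 | *the researcher* | day before surgery, after baseline |

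The first two could be one person under two titles. The third cannot be squared with them if *the researcher* in 4.5 is the person so labelled in 4.4 (blinded outcome collector) and 4.8 (baseline collector). Nothing in the article separates these uses. Section 4.4 also says that few people will deal with patients, so overlapping roles are a practical possibility.

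**2. Timing**

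Section 4.5 places baseline before randomisation twice, once in the sentence quoted and once in the timeline. Only the clinic-visit phrase, together with envelopes tied to enrolment, leaves room for another order. Section 4.3.1 defines elective surgery as taking place the day after the initial evaluation, so the clinic visit may itself be the day before surgery. The text is ambiguous here and does not state the wrong order.

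To show what the ambiguity could cost, suppose that knowing the arm moves baseline by δ in one arm and leaves the post-session score alone. With ANCOVA slope β, the adjusted contrast shifts by β × δ in size. Both inputs are assumptions, not figures from the article:

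- β = 0.5, δ = 1: 0.5 × 1 = 0.5 points
- β = 0.8, δ = 3: 0.8 × 3 = 2.4 points

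Against the 8-point target in section 4.3.1, that is about 6% to 30%. The direction depends on which arm moves.

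**3. Predictability of a fixed block of 6**

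Inputs from the article: three arms, block of 6, 50 per arm, 150 in total. Hence 2 + 2 + 2 per block and 150 / 6 = 25 complete blocks, which agrees with 25 × 2 = 50 per arm. The article gives no predictability figure to reproduce.

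There are 6! / (2! 2! 2!) = 90 equally likely orderings. An allocation is certain when only one arm has places left.

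- Positions 1 to 4: never certain, because at least three places remain and no arm holds more than two.
- Position 5: certain when the last two places belong to the same arm. Given one of them, 1 of the other 5 places matches, so the probability is 1/5.
- Position 6: always certain.

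Expected certain allocations per block = 1 + 1/5 = 1.2. Share = 1.2 / 6 = 20%. Over 25 blocks: 25 × 1.2 = 30 of 150.

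The chance that the best guess is right, by position, is 1/3, 2/5, 1/2, 8/15, 3/5 and 1. The mean is 101/180 = 56.1%, against 33.3% by chance.

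**4. An observer who sees only headset or no headset**

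The block then looks like 2 control and 4 VR. VR versus control is certain from a given position when all remaining places are of one kind:

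- Position 3: 1/15
- Position 4: 1/5
- Position 5: 1/15 + 6/15 = 7/15
- Position 6: 1

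The sum is 26/15 per block. The share is (26/15) / 6 = 28.9%, or about 43 of 150. This observer knows less (VR or not, rather than which VR) but knows it more often.

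**5. Other fixed sizes, same definition as step 3**

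A known block of 3 gives 1/3 (33.3%) and a known block of 9 gives 1/7 (14.3%). Enlarging a known block helps only modestly. Most of the protection comes from the observer not knowing where a block ends.

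**The case against.** The strongest defence is that the sections can be read together as one workable sequence on the day before surgery: consent, baseline, envelope, session. Section 4.5 fixes that order, section 4.3.1 allows the clinic visit to fall on that day, and section 4.7.2 allows preoperative assessment at the moment of recruitment. This largely stands. A reader might infer that baseline STAI-S is taken after allocation and that the primary contrast is biased. The article does not support that. It supports only that one phrase leaves the order open.

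On the allocator, *the researcher* may be a loose label for different people, and section 4.4 requires independence and blinding in plain terms. This stands to the extent that nobody can conclude the blinded assessor is in fact the allocator. It does not remove the conflict in wording. Since STAI-S is self-reported, an unblinded collector also matters less for the primary outcome than for an observer-rated one, though section 4.4 has this person conducting interviews.

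On the block, a fixed size contradicts nothing in the article, and sensible safeguards are present: an outside statistician, opaque sealed envelopes, few staff in contact with patients, a separate room, and patients asked not to discuss allocation. The two VR arms use the same type of device, so knowing the exact arm means knowing the content shown. Publication of the block size does not show that recruiters know it. A reader might infer that one allocation in five is predictable outright, or that the trial is open-label. The 20% is conditional on tracking the block. The article says only that participants are not fully blinded, and it claims blinded assessors and analysts. The shared headset is only a partial answer, because the coarser VR-or-not deduction needs no knowledge of content.

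**Conclusion.** The point holds in this form. The article contradicts itself on who allocates, and on one reading the allocator is the person who must be blind. The order of allocation and baseline is ambiguous because of the clinic-visit phrase, with the weight of the text favouring baseline first. No bias in the primary contrast is shown.

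The block finding is exact but conditional: 20% of allocations (about 30 of 150) are certain to someone who knows the block size, the block boundaries and every previous arm in the block. It assumes one unstratified list at one centre, as the article implies. It is an avoidable weakness in the design, separate from the contradiction. These matters should be corrected, but they do not by themselves undermine the trial.

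**What to change.** 1. Describe one procedure in sections 4.4 and 4.5. A named role, with no part in recruitment or outcome collection, opens the next envelope only after baseline STAI-S and VAS are completed and recorded on the day before surgery.
2. Remove the clinic-visit timing from section 4.4 and the statement in section 4.5 that has the researcher allocate. Use one title for the independent person throughout, and distinguish that role from the data collector in section 4.8.
3. For patients not yet enrolled, have the outside statistician generate a new list with randomly varying block sizes in multiples of 3, such as 6 and 9, not disclosed to site staff.

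**Cost.** Items 1 and 2 are wording and use a role that the article already provides for. Item 3 needs a new list. The article does not give recruitment status, so the number of patients it would cover is unknown. If recruitment stops inside a block, two arms could differ by up to 3 patients from a block of 9, or 2 from a block of 6. No outcome, sample size or element of care changes.

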### 4.6. VR Device

For the intervention group, the Oculus Meta Quest 2 Goggles device (Meta Platforms, Inc., Menlo Park, CA, USA) will be used. It is an advanced and immersive HMD with ultra-short-focus optical technology. The VR device comes with a precision controller that acts as a natural extension of one’s hands. Improved tracking capabilities mean that it can also be operated controller-free. These features are designed to effectively address blurring at the edges of the field of view to reduce dizziness and improve user comfort and immersion.

### 4.7. Intervention in Each Group

#### 4.7.1. VR Intervention Group

The day before the surgery, the VR procedure will be explained to the patients while they wait for surgery. The VR group will be exposed to a unified 10 min VR video via Meta Quest 2 Goggles after receiving routine standard care. A 360° video with an immersive audio–visual environment describing the preoperative and postoperative experience on the day of the surgery will be provided, by which the patients can get accustomed to the environment and procedures associated with the surgery. Background audio will be provided through headsets, and the video will be directed by a neurosurgeon filmed using a Max 360 action VR camera (GoPro, Inc., San Mateo, California, USA). In the video, actors, neurosurgeons, and nurses will re-enact a typical day for a mock patient undergoing surgery, plus routine postoperative care, including the postoperative immediate recovery room and rehabilitation care by neurosurgeons, psychologists, and physiotherapists in the ward. Patients are allowed to move around freely so that they can experience all aspects of the virtual space, and are encouraged to ask questions at the end.

#### 4.7.2. VR Relaxation/Distraction Intervention Group Patients

The VR relaxation/distraction intervention group will be provided with standard routine care followed by a VR intervention designed to facilitate relaxation and distraction. This intervention utilizes numerous highly immersive environments, each stimulating a distinct natural setting (i.e., natural landscapes, urban parks, tropical beaches and forests) with background music, delivered via a commercially available application (i.e., Nature Treks VR (Greensky Games, London, UK), accessed via the Meta Quest platform (Meta Platforms, Inc., Menlo Park, CA, USA)) through a head-mounted display (HMD) and headsets. Patients can navigate these environments using a handheld controller, engaging in context-specific activities such as walking along a beach or climbing a mountain. These interactions are accompanied by dynamic environmental changes, which enhance the sense of presence, facilitate immersive engagement, and contribute a vivid experience.

These interventions will be delivered and preoperative assessment will take place on the day before surgery or at the moment the patient is recruited. Additionally, the postoperative assessment will be conducted within 24 h after the operation. The rationale for comparing both interventions is to explore whether cognitive (information-based) or emotional (relaxation-based) mechanisms provide greater benefit in the perioperative context.

We aimed at assessing the value of educational and exposure to stress factors in comparison to the second (2nd) intervention, where we use various relaxing immersive and game-based destinations that patients have access to prior to their respective surgeries.

#### 4.7.3. Standard Care (Control) Group

In the standard group, patients will only receive standard care and be provided with routine descriptions of the preoperative experience, where a surgeon will explain to them what the preoperative experience will entail.

After VR intervention, psychometric assessments of anxiety, pain score, and satisfaction will be performed and evaluated shortly before the intended surgery. Subsequently, the patients will undergo their planned surgical procedure. Postoperative data on analgesic use and pain will also be collected in the recovery area.

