
## 1. Background

Preoperative anxiety and stress are a frequently encountered phenomenon among patients, while such anxiety is experienced on different levels based on sociodemographic characteristics. The overall prevalence of preoperative anxiety varies and is reported in a range of 60–80% while other studies showed a wider range of 11–80% [1,2,3,4,5]. It occurs as a compatible and physiological response to surgical encounters and stress, which might occur anytime preoperatively [6]. The anxiety and stress are induced during hospitalization and intensified when a patient is informed about the need to undergo surgical intervention, and shortly before surgery [7].

Preoperative stress-related signs are associated with a potential change in patients’ psychological responses and hemodynamic parameters, including increased blood pressure and heart rate, that may pose a danger to the patients’ health [8]. Thus, these changes might affect the quality of anesthesia and demand for analgesics, postoperative pain, and possible delirium [9].

It also has significant impact on recovery, including longer postoperative hospital stay and even cognitive and behavioral ramifications. Thus, procedures which are painful lead to preoperative and postoperative anxiety, which causes fear in patients. This leads to a reduced pain threshold and higher postoperative pain and can affect patients’ compliance with subsequent future procedures [10]. A meta-analysis revealed that social support is crucial in reducing the postoperative anxiety among patients undergoing elective surgery. Conventional methods and interventions for managing pain and anxiety typically involve patient education and therapy with anti-anxiety medications prior to surgery to enhance patients’ comfort. However, randomized controlled trials have reported that these approaches provide only limited effectiveness and are associated with risks such as side effects, dependence, drug tolerance, and prolonged recovery time. As a result, there is increasing demand for non-pharmacological interventions to manage pain and anxiety, mitigating the drawbacks and risks associated with this traditional approach [11,12].

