#### 4.7.4. Clinical Outcome Variables and Assessment

The primary outcome is the change in STAI-S score from baseline to immediately after intervention. Secondary outcomes include postoperative pain intensity assessed using the Visual Analogue Scale (VAS), postoperative analgesic use, patient satisfaction, and VR-related adverse effects. These outcomes will be measured preoperatively on the day before surgery, before the VR content exposure, and after. Measurements will be made again postoperatively—within 24 h. Preoperative and postoperative STAI-S and VAS will be compared for data analysis.

The baseline assessment is conducted one day before surgery, prior to the VR intervention, to capture the patient’s preoperative state under conditions closest to the actual surgical context. We believe this timing best reflects the anxiety and pain levels that the VR intervention aims to reduce. The postoperative assessment within 24 h is intended to evaluate the immediate effect of the intervention on perioperative anxiety and pain, which is the primary focus of our study. We acknowledge that longer-term outcomes may differ, but these are beyond the scope of the current trial, which specifically targets the short-term perioperative period (see Table 2).

The secondary outcome will be the patients’ quality of life and satisfaction (EVAN-G) of the VR intervention, time spent thinking about pain assessed, and postoperative analgesics measured from patient treatment charts within 24 and 48 h postoperatively and used for data analysis, as the level of satisfaction and thinking time spent on pain can contribute to an increased perception of pain.

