### 4.9. Statistical Analysis

The statistical analysis will be performed under the mentorship of a biostatistician experienced in neurosurgical research. The nominal data will be presented as *n* (% of the total). The dependencies between them will be assessed using the test chosen based on the size of the smallest sample. All analyses will follow an intention-to-treat approach. The primary endpoint (change in STAI-S score from baseline to immediately postintervention) will be analyzed using one-way ANCOVA adjusted for baseline STAI-S. Pairwise comparisons will be Bonferroni-corrected. Secondary outcomes will be analyzed as follows: VAS pain at 24 h (ANCOVA adjusted for opioid dose), total opioid consumption (ANOVA or Kruskal–Wallis depending on distribution), patient satisfaction (Kruskal–Wallis), and rescue analgesic use (χ^2^ test). Longitudinal measures (baseline → post-VR → postoperative) will be evaluated with a linear mixed-effects model including group, time, and group × time interaction. Normality will be tested using the Shapiro–Wilk test. Missing data will be assessed for pattern and mechanism. Multiple imputation (m = 10) will be used if appropriate. Longitudinal analyses will primarily rely on linear mixed-effects models, which are robust to missing observations under missing-at-random assumptions. The primary comparison will evaluate procedural/educational VR versus standard care with respect to STAI-S score change. Secondary comparisons will include relaxation/distraction VR versus standard care and procedural/educational VR versus relaxation/distraction VR. Postoperative pain analyses will additionally be adjusted for perioperative opioid consumption and surgery duration when appropriate. Statistical analysis will be performed using STATISTICA 13.1 (TIBCO, Palo Alto, Santa Clara, CA, USA) and two-sided α = 0.05.

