## Figures and Tables

**Table 1 brainsci-16-00587-t001:** Eligibility Criteria for Study Enrollment.

Inclusion Criteria	Exclusion Criteria
Adult patients between 18–70 years old Patient’s admission prior to surgery day (at least 1 day) Patients’ first surgery with no prior surgical history cervical vs. lumbar vs. thoracic) Type of spine surgery (e.g., cervical vs. lumbar vs. thoracic) Surgical approach (e.g., minimally invasive vs. open) Anesthetic technique (e.g., general) Expected hospital stay—2 days Capable of providing informed consent and participate in the study follow-up questionnaire Patients speak English	Congestive heart failure, hypertension and anti-hypertensive medications Adrenal insufficiency Cognitive impairment (evaluated by MMSE, MoCA) Cerebrovascular diseases, ophthalmological diseases (strabismus, diplopia, retina degeneration, glaucoma), neurological conditions (epilepsy or seizure, dementia, vertigo, dizziness, motion sickness)—evaluated by: history taking, examination, vision test (Ishihara test) Auditory impairment Psychiatric illness (schizophrenia, bipolar disorder, psychotic depression)—(evaluated by MINI questionnaire) Patients with neuropathic pain Use of sedative drugs, anti-depressants, anxiolytics, and anti-epileptic drugs Claustrophobia GCS < 15

**Legend:** MMSE, Mini-Mental State Examination; MoCA, Montreal Cognitive Assessment; MINI, The Mini International Neuropsychiatric Interview; GCS, Glasgow Coma Scale.

**Table 2 brainsci-16-00587-t002:** Primary and secondary outcome assessment.

Timepoint	Assessment	Measures
Day before surgery (pre-VR)	Baseline	STAI-S, VAS pain
Day before surgery (post-VR)	Immediately after VR intervention	STAI-S, VAS pain, patient experience satisfaction
Within 24 h after surgery	Postoperative	VAS pain, analgesic use

**Table 3 brainsci-16-00587-t003:** Preoperative and postoperative psychometric scales.

Baseline Values
Patients’ demographics: age, sex, education, medical history (comorbidities), medication, surgery type, duration, ASA status Anxiety (STAI-S) Stress (PSS-10) Depression (BDI-II) Pain score (VAS) Satisfaction (EVAN-G) Cognitive (ACE-III) Personality test (PID-5) Postoperative analgesia (Medical charts and records)

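### The second STAI-S of the primary endpoint is given two conflicting times, and its anchor does not secure equal elapsed time from baseline in the control and VR arms

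*Protocol article*

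**What the plan says.** **Endpoint and its time.** Section 4.7.4 states: "The primary outcome is the change in STAI-S score from baseline to immediately after intervention". Section 4.9 analyses the same quantity, "change in STAI-S score from baseline to immediately postintervention", by ANCOVA adjusted for baseline STAI-S. It names procedural/educational VR versus standard care as the primary comparison. Table 2 has one row between the VR session and surgery. That row is dated the day before surgery, labelled "Immediately after VR intervention", and lists STAI-S, VAS pain and satisfaction. The timeline in Section 4.5 runs "VR or standard-care intervention on the day before surgery → immediate postintervention assessment → surgery".

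**The conflicting sentence.** Section 4.7.3 describes the control arm. It says that after the VR intervention "psychometric assessments of anxiety, pain score, and satisfaction will be performed and evaluated shortly before the intended surgery", and that patients then go on to their operation.

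**What each arm receives.** Under Sections 4.7.1 and 4.7.2, both VR arms get standard care first and VR afterwards; the educational video lasts 10 minutes. Section 4.7.3 gives controls standard care only, with no stated length or end.

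**The trial's premise about anxiety.** The Background says that anxiety is "intensified when a patient is informed about the need to undergo surgical intervention, and shortly before surgery".

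**The concern.** State anxiety depends on when it is measured. On the protocol's own account it rises as the operation approaches, so a score taken directly after a session on the day before surgery and a score taken close to the operation measure different states.

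Two things follow. First, staff working from Section 4.7.3 and staff working from Table 2 could take the primary measurement at different times. Second, even if everyone follows Table 2, its anchor is an event that controls do not have. If the second score falls at different elapsed times by arm, the resulting anxiety difference becomes part of the estimated VR effect. It arises after randomisation and after baseline, so neither randomisation nor the baseline covariate removes it. It cannot be undone at analysis once the scores have been collected.

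**Working it through.** **1. Is Section 4.7.3 describing an extra assessment?** Its items are anxiety, pain and satisfaction. Table 2's post-VR row lists STAI-S, VAS pain and satisfaction, and Table 2 has no other row between VR and surgery. The two places describe one assessment. Section 4.4 puts the VR session on the day before surgery, so directly after VR and close to the operation do not naturally coincide.

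**2. What fixes the time in controls?**

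| Place | Time of second score | Covers controls? |
|---|---|---|
| 4.5 timeline | Directly after VR or standard care, day before surgery | Yes, by order of events |
| 4.7.4 and 4.9 | Directly after the intervention | Yes, if standard care counts as the intervention |
| Table 2 | Directly after VR, day before surgery | Not as worded |
| 4.7.3 | Close to surgery, after VR | Unclear: control heading, VR wording |

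**3. Does the same order give the same elapsed time?** Let s be the length of standard care, o the VR orientation and v the VR session, with the baseline score first as in the Section 4.5 timeline.

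- Controls: elapsed time = s
- VR arms: elapsed time = s + o + v
- Difference = o + v

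For the educational arm v = 10 minutes, so the literal difference is at least 10 minutes plus orientation. That assumes s is equal across arms, but s and o are not stated. If one arm followed Section 4.7.3 and the other Table 2, the gap would run from one day into the next. No clock times are given.

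**4. What could a shift do?** The documents give no figure for STAI-S drift, so the shift b is an assumption. Inputs from Section 4.3.1 are an 8-point target, SD about 10 and 42 per arm. From Section 4.9, two-sided α is 0.05.

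The 42 does not reproduce from these inputs: 2 × (1.960 + 0.842)² × 10² / 8² = 24.5, so 25 per arm, or 33 at α = 0.05/3. The stated number is the larger, and the timing point does not depend on it. I use 42 as given.

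- SE of the difference = 10 × √(2/42) = 2.18
- Share of target: 2/8 = 25%; 4/8 = 50%
- Rejection rate with no true effect = Φ(b/SE − z) + Φ(−b/SE − z), with z = 1.96 at α = 0.05
- Power when the shift opposes a true 8-point effect: the same formula with 8 − b in place of b

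| Assumed shift b | Rejection, no true effect, α = 0.05 | Same, α = 0.05/3 | Power at 8 points if shift opposes VR, α = 0.05 |
|---|---|---|---|
| 0 | 5% | 1.7% | 96% |
| 1 | 7.4% | 2.9% | 89% |
| 2 | 15% | 7.0% | 79% |
| 4 | 45% | 29% | 45% |

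These figures show sensitivity to timing. They do not estimate the bias in this trial.

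**The case against.** The strongest reply is that the endpoint is defined consistently wherever it is formally defined. The abstract, Sections 4.7.4 and 4.9, the timeline and Table 2 agree, and one narrative sentence in Section 4.7.3, which names neither STAI-S nor the primary endpoint, is the outlier. It may loosely mean the preoperative phase. This stands as a reason to expect an easy correction. It does not remove the conflict, because the sentence covers the same three measures at another time.

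Four stronger readings are tempting, and the documents do not support them.

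- **Controls have no assessment slot.** The Section 4.5 timeline names standard care and gives it an immediate assessment on the day before surgery. What it lacks is a matched elapsed time. A condensed article may leave minute-level detail to the full protocol, but the VR-only label in Table 2 is part of the stated text.
- **There is a third conflicting time.** Section 4.7.2 says "preoperative assessment will take place on the day before surgery or at the moment the patient is recruited". Section 4.3.1 defines elective surgery as the day after initial evaluation, and Sections 4.5 and 4.8 put consent and baseline on the day before surgery, so the two alternatives largely coincide. The sentence also concerns preoperative assessment in general.
- **Controls are assessed in a worse setting.** Section 4.4 says "In the experiment room, the patients will be exposed to VR content, with respective psychological and physiological assessments" and is silent on where controls are assessed. Silence does not show a difference.
- **The bias favours VR.** No passage plans different times by arm. Read by its heading, Section 4.7.3 moves controls later, which on the Background's premise would flatter VR. Read by its opening words, it moves VR patients later, which would count against VR.

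**Conclusion.** The point holds in a limited form. Section 4.7.3 contradicts the timing of the primary measurement given in Sections 4.5, 4.7.4 and 4.9 and Table 2. Separately, the post-intervention anchor does not secure equal elapsed time from baseline, because standard care has no defined end, VR follows standard care in the VR arms, and Table 2 refers to VR alone. Unequal timing is a possibility that the text leaves open; it is not a stated plan.

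The size and direction of any resulting bias are unknown from the documents. The 25% to 50% share of the 8-point target rests wholly on an assumed shift of 2 to 4 points, and the error rates rest further on SD 10 and 42 analysed per arm. The qualitative conclusion needs none of these figures: a timing difference that affects anxiety passes point for point into the primary estimate, and baseline adjustment cannot take it out.

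**What to change.** - Reconcile Section 4.7.3 with Sections 4.5, 4.7.4 and 4.9 and Table 2, so that there is a single primary STAI-S time point on the day before surgery.
- Reword the Table 2 row so that it refers to the intervention or control period and covers all three arms.
- Take the second STAI-S in controls at the same elapsed time from baseline as in the VR arms, and in the same setting.
- Record the actual time of each STAI-S, so that balance between arms can be shown.
- If a STAI-S close to surgery is wanted, make it a separate secondary outcome collected in every arm.

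The cost is a protocol wording change, a time field on the case report form and a short timed assessment slot for controls.
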